#### Limited Efficacy

Bivariate testing will be conducted to assess whether the intervention and control groups are balanced on key characteristics, including demographics, baseline asthma control (based on Child Asthma Control Test score on enrollment), and baseline medication adherence. If the groups are balanced, differences in 30-day adherence proportions and parental perceptions of asthma control between the intervention and control groups will be assessed using *t* tests or Wilcoxon Mann-Whitney tests depending on the distribution of the data. If the groups are unbalanced, regression models will be used to adjust for the unbalanced measured confounders.

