### Participants – Inclusion and Exclusion Criteria

Participants will include 40 children aged 2 to 13 years and their parent or legal guardian. To be enrolled in the study, children and their parent or legal guardian must meet the following eligibility criteria: (1) they must be receiving care for asthma on the ED or inpatient asthma pathways; (2) they must have been prescribed a daily ICS or combined ICS or long-acting beta agonist (LABA) in the year prior to the current admission and the ICS prescribed on discharge must be an MDI compatible with the electronic monitoring sensor (compatible ICS and ICS or LABA medications include Flovent [fluticasone], QVAR [budesonide], Advair MDI [fluticasone-salmeterol], Dulera [mometasone-formoterol], and Asmanex [mometasone-furoate]); (3) children and families must live or receive primary care in Philadelphia ZIP codes with the highest child asthma morbidity (greater than 100 pediatric asthma hospitalizations per year, according to Pennsylvania Health Care Cost Containment Council [22] hospitalization data); and (4) the parent or legal guardian must have a mobile phone plan with unlimited text messages.

Children will be excluded from the study if they are prescribed a controller inhaler to which the electronic device cannot affix (eg, any dry powder inhaler, Symbicort [budesonide or formoterol], or Seretide [fluticasone-salmeterol]) as their primary controller medication. Children with comorbid conditions that may influence the treatment of asthma (such as chronic lung disease, structural heart disease, or cystic fibrosis) will be excluded. Families will be excluded from the study if they have active state social services involvement or if they are non-English speaking. Subjects with significant developmental delays will also be ineligible.

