#### Adherence Trajectories

Finally, we will perform an exploratory analysis to assess for discrete trajectories of adherence using group-based trajectory modeling (GBTM). This analysis will include data from both the intervention and follow-up phases of the study. If no significant differences exist in limited efficacy outcomes between the intervention and control groups, data from both groups will be combined to produce pooled trajectory outcomes.

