### Intervention

#### Enrollment

Potential subjects will be screened through the daily census listings for the ED and general pediatrics inpatient units at CHOP, using the protocol inclusion and exclusion criteria. Parents of eligible participants will be approached for informed consent, screening, and enrollment prior to the patient’s discharge from the hospital. Child assent will be obtained from children ages 7 years and older, unless the child is judged to be incapable of assent. If subjects provide consent and enroll, they will complete the initial study visit prior to hospital or ED discharge. As part of enrollment, caregivers will complete an initial 30-minute survey on the Way to Health (WTH) platform (see below for description). Prior to survey completion, participants will be randomized into either the control or intervention group using a 1:1 randomization scheme, stratified by location (ED or inpatient). Each participant will be compensated US $20 through a reusable debit card following completion of each survey, for a total of US $60 for those completing the entire study.

Following the baseline survey, a study team member will attach an electronic sensor to the participant’s ICS inhaler. If the participants do not have a currently filled ICS prescription with them in the hospital room, they will be instructed on how to attach the sensor to the child’s inhaler when they get home. Participants whose sensors are not attached to the inhaler at discharge will be contacted by phone to achieve an initial sync. Participants who have mobile phones will download the Propeller mobile phone app for data transmission purposes, but the participants will not have access to any information from the app. Preferences for the text messages, which are delivered to the parents’ mobile phone via the Way to Health platform (time of day and preferred phone number), will be collected for all participants. Participants will be instructed to use the inhaler as directed by their physician and that they may begin to receive automated text message reminders regarding their child’s medication use.

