### Limitations

We anticipate several limitations of this study. Since the study is oriented to feasibility, the study is not powered to detect between-groups differences in adherence or adherence trajectories. Differences in actuation data, parent perception of asthma control, and medication use trajectories will be evaluated to assess trends for future efficacy testing.

Given the vulnerable nature of the patient population, researcher’s ability to contact caregivers for follow-up calls will limit both completion of the intervention and follow-up surveys and ongoing syncing. Many parents have changing work schedules that make it difficult to predict availability for follow-up calls in advance. Parents also frequently change their primary phone numbers, which limits follow-up and may affect whether they receive the text message intervention for the entire study period. We will reduce this limitation by asking participants for multiple contact numbers and recording preferred times to receive calls.

Most families in this study will go home with a new ICS prescription at discharge, however, the prescription is not always filled at the on-site pharmacy, so the sensor will not always be applied by study staff. In this circumstance, the caregiver must successfully fill the prescription at their pharmacy and correctly attach the electronic sensor themselves in order for actuation data to be available. To address this concern, research staff will conduct reminder calls in the few days following discharge. As a result of this limitation, actuation data at the front end of the intervention phase may be missing for some participants.

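### Efficacy in this 40-child pilot is to be assessed by significance tests with no stated interval or SD, and a non-significant result triggers pooling of the arms

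*Protocol article*

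**What the plan says.** All references are to the protocol article.

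- **Outcomes.** Outcome Measures makes feasibility primary. The two limited efficacy outcomes are 30-day percent ICS adherence from the sensors and change in parent-reported asthma control. The Limited Efficacy part of that section plans an average for each arm on each outcome.
- **Analysis.** In Data Analysis, Limited Efficacy, the rule for balanced arms is that "differences in 30-day adherence proportions and parental perceptions of asthma control between the intervention and control groups will be assessed using" one of two significance tests. The first is the t test; the alternative is given as "Wilcoxon Mann-Whitney tests depending on the distribution of the data". For the remaining case, regression is named: "If the groups are unbalanced, regression models will be used to adjust for the unbalanced measured confounders". No confidence interval or SD is mentioned for either outcome.
- **Power and purpose.** Limitations states that "the study is not powered to detect between-groups differences in adherence or adherence trajectories", and that differences in actuation data, perceived asthma control and trajectories "will be evaluated to assess trends for future efficacy testing".
- **Use of the test result.** Adherence Trajectories says: "If no significant differences exist in limited efficacy outcomes between the intervention and control groups, data from both groups will be combined".
- **Size.** "Participants will include 40 children aged 2 to 13 years and their parent or legal guardian". The Enrollment section gives 1:1 allocation.

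**The concern.** The named tool does not fit the stated purpose. To plan a later efficacy trial one needs the size of the difference, its uncertainty and the spread of the outcome. A p-value from about 20 children per arm supplies none of these. On the Wilcoxon branch, the p-value does not refer to the quantity that the article defines as the outcome, which is a difference in average adherence.

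The pooling rule makes this more than a matter of reporting style. It treats non-significance, in a comparison that the article itself calls underpowered for adherence, as sufficient reason to merge the arms for the trajectory analysis. If the reminders do have a moderate effect, the pooled trajectories would mix treated and untreated patterns without saying so. The later trial would also inherit a verdict of no significant difference instead of a range of plausible effects.

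**Working it through.** **Inputs from the article.** 40 children allocated 1:1, so n = 20 per arm. The article gives no alpha, target difference, SD or expected loss, so there is no power figure to reproduce.

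**Assumptions.** Two-sided alpha 0.05; SD of percent adherence 25 to 35 points; 14 to 20 evaluable children per arm (20 × 0.7 = 14 at 30% loss). The calculations are for the t test.

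**1. Precision of the difference.** Half-width of the 95% CI = t(0.975, 2n − 2) × SD × √(2/n).

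| n per arm | in SD units | SD 25 | SD 30 | SD 35 |
|---|---|---|---|---|
| 20 | 0.64 | 16.0 | 19.2 | 22.4 |
| 14 | 0.78 | 19.4 | 23.3 | 27.2 |

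The t test is significant only when the observed difference exceeds this half-width. At SD 30 and 20 per arm, an observed gain of 19 points would be non-significant, and its interval would run from about 0 to 38 points.

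**2. Power.** Noncentral t with noncentrality δ / (SD × √(2/n)).

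| True effect (SD) | n = 20 | n = 14 |
|---|---|---|
| 0.2 | 10% | 8% |
| 0.3 | 15% | 12% |
| 0.5 | 34% | 25% |
| 0.8 | 69% | 53% |
| 0.9 | 79% | 63% |
| 1.0 | 87% | 72% |

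Power of 80% needs a true effect of 0.91 SD with 20 per arm and 1.10 SD with 14. In adherence points with 20 per arm, at SD 25, 30 and 35:

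- a true 15-point gain has 46%, 34% and 26% power;
- a true 25-point gain has 87%, 73% and 60% power.

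**3. What the pooling rule does with this.** At a true effect of 0.5 SD, the adherence test is non-significant with probability 1 − 0.34 = 66% (20 per arm) or 1 − 0.25 = 75% (14 per arm). Pooling also requires no significant difference in asthma control, so these are upper limits on the chance of pooling in that case.

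**4. Why the SD matters for the next trial.** For 80% power to detect 15 points, n per arm = 2 × (1.96 + 0.84)² × (SD/15)². This gives 44, 63 and 86 at SD 25, 30 and 35, so the top of the assumed range needs nearly twice the trial of the bottom (86/44 = 1.95). The pilot can estimate this quantity: with 38 degrees of freedom, the 95% CI for a pooled SD runs from 0.82 to 1.29 times the estimate.

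**The case against.** The strongest reply is that this is a condensed article. It names the comparison method and does not say that only p-values will be reported, and intervals and SDs are commonly left to a fuller plan. That would dispose of the point if silence on intervals were all there was. It does not cover the pooling rule, which is a stated decision resting on non-significance. Nor does it remove the mismatch between a test as the stated assessment and a purpose that calls for estimation.

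Three further objections stand and limit the point:

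- A reader might infer that the plan yields no effect size. It does not go that far. Outcome Measures plans a difference in average adherence, per-arm averages are specified, and the regression branch would give an adjusted difference. What is unstated is the interval and the spread.
- A reader might infer that a finding of no difference is the expected result. That depends on an effect size and SD that the article does not give. The Introduction cites very large gains in two earlier trials, and an effect near 0.9 SD or above would usually be detected with 20 per arm. The Introduction also says effectiveness in this population is unknown and that the causes of nonadherence go beyond forgetting, so a moderate effect is plausible too.
- A reader might express the half-width relative to the 11–37% background adherence in the Introduction. The lower end of that range does not support it. On a 0–100 scale with mean 11, the SD cannot exceed √(11 × 89) ≈ 31, so SD 30 there would mean almost all-or-nothing use. The article also gives no expected control value for the month after discharge.

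Finally, the sentence on power names adherence and trajectories, not asthma control. The same 20 per arm applies to asthma control, but the article does not itself declare that comparison underpowered.

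**Conclusion.** The concern holds in a limited form. The analysis section assesses the efficacy outcomes by tests that suit their stated use poorly, states no interval or SD, and lets non-significance decide whether the arms are merged. With 20 per arm the 95% CI extends 0.64 SD either side of the estimate, or 16 to 22 points under an assumed SD of 25 to 35. True effects of about 0.5 SD or less would usually be missed (power about 34% at 0.5 SD), while those of about 0.9 SD or more would usually be found. The SDs, two-sided alpha of 0.05 and evaluable numbers are assumptions, but the half-width in SD units depends only on the number per arm.

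The change is worth making but does not threaten the study. Efficacy is labelled limited, the lack of power for adherence is disclosed, and no primary feasibility conclusion depends on these tests.

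**What to change.** In Data Analysis, Limited Efficacy:

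- Make the main result for each outcome the between-group difference (intervention minus control) with a 95% CI, for 30-day percent adherence and for change in asthma control. If the data are clearly skewed, use a bootstrap interval for the same difference in means, so that the quantity estimated does not change with the distribution.
- Report the mean and SD per arm for both outcomes. If the regression branch is used, report the adjusted difference with its 95% CI as well.
- Give p-values, if at all, as secondary, and state that a non-significant result will not be read as no effect.

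In Adherence Trajectories, remove non-significance as the trigger for pooling and fix the approach beforehand. One option is to fit the model to all children whatever the tests show and tabulate trajectory-group membership by arm, labelled exploratory.

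The cost is analysis and reporting wording only. No data collection, sample size or primary outcome changes. The intervals will be wide, and the report should say so.

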#### Limited Efficacy

Limited efficacy outcomes for this study will include (1) percent ICS adherence, as measured by electronic monitoring and (2) average change in parent-reported asthma control, assessed using the parent-reported portion of the child Asthma Control Test [25]. Inhaled controller medication use will be measured in both groups using electronic sensors (see description below) affixed atop of the MDI canister. ICS adherence will be calculated from the daily medication use data as the average percent adherence (observed actuations or prescribed actuations) for the intervention group versus the control group for the 30-day intervention phase. The average change in the parent-reported portion of the child Asthma Control Test score between enrollment and the 30-day follow-up call will be calculated for the intervention and control groups.

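### Baseline significance tests decide whether and how the efficacy comparison is adjusted; one pre-specified model per outcome, with stratum and baseline value, would be fixed in advance and at least as precise

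*Protocol article*

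**What the plan says.** The relevant rules stand in three sections of the protocol article.

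- **Data Analysis, Limited Efficacy.** The first step is a check of the arms at baseline: "Bivariate testing will be conducted to assess whether the intervention and control groups are balanced on key characteristics". The variables named for this check are demographics, the enrollment asthma control score and prior adherence; no threshold for balance is given and the list of variables is open. If the arms count as balanced, differences in 30-day adherence and in perceived asthma control "will be assessed using *t* tests or Wilcoxon Mann-Whitney tests depending on the distribution of the data". The other branch reads: "If the groups are unbalanced, regression models will be used to adjust for the unbalanced measured confounders".
- **Intervention, Enrollment.** Participants are "randomized into either the control or intervention group using a 1:1 randomization scheme, stratified by location (ED or inpatient"). Location is not among the named baseline characteristics and appears in no stated model.
- **Outcome Measures, Limited Efficacy.** Adherence is the average percentage over the 30-day intervention phase, with no baseline term. For asthma control, "The average change in the parent-reported portion of the child Asthma Control Test score between enrollment and the 30-day follow-up call will be calculated", so the enrollment score enters by subtraction.

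The sample is given under Participants: "Participants will include 40 children aged 2 to 13 years and their parent or legal guardian", hence about 20 per arm. The Limitations section says that the study is not powered for between-group differences, which will be read as trends for future efficacy testing.

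**The concern.** In a randomised comparison a baseline p-value measures only the play of chance. It says nothing about whether a variable predicts outcome, and that is what decides whether adjustment is worthwhile. A rule that adjusts only for variables that reach significance will therefore usually leave out a useful predictor and will sometimes bring in an irrelevant one. The choice between a mean comparison and a rank test is also left to the data, so the model, the covariates and the test statistic are all open until the results are seen.

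At stake is the quality of the between-arm estimates that the pilot hands on to a later efficacy trial. There is also a knock-on effect. Under Adherence Trajectories, the arms are pooled for trajectory modelling if these same efficacy outcomes do not differ significantly, so a noisier or conservative test makes pooling more likely.

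**Working it through.** The article gives no power calculation, effect size or SD for these outcomes, so there is no figure of the plan's own to reproduce.

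**Inputs from the article:** 40 children, 1:1, so n = 20 per arm; stratification by ED or inpatient; the two-branch rule; the change-score definition.

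**Assumptions:** two-sided 0.05 for each balance test; baseline-outcome correlation ρ from 0.2 to 0.7; normally distributed outcome; an ED/inpatient outcome difference of 0.3 to 0.8 SD.

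**1. What a balance test can flag.** The smallest flagged observed difference is t(0.975; 38 df) × √(2/20) = 2.024 × 0.316 = 0.64 SD. An observed 0.5 SD imbalance gives t = 0.5/0.316 = 1.58, p about 0.12, and is not flagged.

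**2. How often each branch is taken.** Under randomisation a single variable is flagged in 5% of trials, so it stays out of the model in about 95%. The Covariates section lists ten demographic items (six for the caregiver, four for the child). Baseline control and baseline adherence bring this to 12. If the tests are independent, the chance of at least one flag is:

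- 10 tests: 1 − 0.95^10 = 0.40
- 12 tests: 1 − 0.95^12 = 0.46

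Correlation among the items would lower these figures.

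**3. Precision.** These results come from 20,000 simulated trials per setting with 20 per arm. The two-step rule (one tested baseline variable) and the change score are each compared with an ANCOVA on arm, baseline and stratum.

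| ρ | Two-step variance ÷ ANCOVA | Change-score variance ÷ ANCOVA | Two-step type I error |
|---|---|---|---|
| 0.2 | 1.01 | 1.63 | 4.9% |
| 0.3 | 1.05 | 1.49 | 5.0% |
| 0.5 | 1.21 | 1.30 | 4.2% |
| 0.7 | 1.69 | 1.14 | 3.5% |

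A large-sample check on the change score: its variance is 2(1 − ρ) against 1 − ρ² for ANCOVA, a ratio of 2/(1 + ρ). This gives 1.67, 1.54, 1.33 and 1.18 for the four values of ρ. The simulated ratios are slightly lower because estimating the ANCOVA coefficients costs a little with 40 children.

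The two columns run in opposite directions. The two-step loss grows with ρ, while the change-score loss is largest when ρ is low.

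**4. Leaving out the stratum.** With strata balanced across arms, the estimate itself is unaffected, but its standard error absorbs the location difference.

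| ED/inpatient difference | Mean SE, stratum omitted | True SD of estimate | Type I error |
|---|---|---|---|
| 0.3 SD | 0.318 | 0.318 | 5.1% |
| 0.5 SD | 0.324 | 0.315 | 4.2% |
| 0.8 SD | 0.339 | 0.318 | 3.5% |

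**The case against.** **Low stakes.** The primary outcomes are feasibility outcomes, the study is openly unpowered for efficacy, and no confirmatory conclusion hangs on these tests. This stands, and it limits the weight of the point.

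**A condensed article.** The covariate list and the use of the stratum are details that an analysis plan commonly supplies. This stands in part: the missing stratum alone would be no finding. The test-then-adjust rule, however, is stated outright, and no later document could name one model in advance without replacing it.

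**The gain may be small.** For adherence, the baseline is a caregiver's recall of the previous four weeks and the outcome is sensor-recorded use. Their correlation may be low, and at 0.2 the loss is about 1%. This also stands. A headline gain taken from a single correlation such as 0.5 would overstate what is known.

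A reader might also infer more than the article supports:

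- **That a true 0.5 SD baseline imbalance is missed in about two-thirds of trials.** Power against such a difference is 34%, but randomisation rules out a true difference between arms. The relevant quantity is the observed imbalance in step 1.
- **That baseline scores are ignored altogether.** This is not so for asthma control, where the enrollment score is subtracted.
- **That the estimand is undefined or the estimate biased.** In a linear model the adjusted and unadjusted mean differences target the same quantity. Only the t-versus-Wilcoxon switch changes what is estimated. The errors found here are conservative, not inflating.

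**Conclusion.** The concern holds in a limited form. The stated rule makes the estimator, the covariates and the test depend on chance, and it is never more precise than a pre-specified ANCOVA at the correlations tried. The size of the loss is not known from the article. For the two-step rule it runs from about 1% of variance at a correlation of 0.2 to about 69% at 0.7, and for adherence it may lie near the low end. For asthma control the change score costs between about 14% and 63%, if the comparison in Data Analysis uses the change defined under Outcome Measures. Omitting the stratum causes no bias, but it gives a standard error that is too large if outcome differs appreciably by location.

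These figures rest on the assumed 0.05 threshold, correlations and location differences, and on all 40 children being analysed. This is an improvement worth making before analysis, of modest severity, and not a flaw that undermines the pilot.

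**What to change.** Drop the balance tests as a decision rule and describe baseline characteristics by arm without p-values. Name one linear model per outcome in advance:

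- **30-day percent adherence** on arm, ED/inpatient stratum and baseline parent-reported adherence.
- **30-day parent-reported asthma control score** on arm, stratum and enrollment score, in place of the raw change comparison.

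Report each adjusted difference with a 95% confidence interval from one inference method fixed beforehand, for example small-sample robust standard errors. The t-versus-Wilcoxon choice then falls away.

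The cost is a change of wording and two degrees of freedom per model. All the variables are already collected, and the Results section describes the study as ongoing with analysis still to come. No larger sample is needed.
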